## Methods/design

### Adaptation of a diabetes prevention curriculum for *EPIC El Rio Families*

The intervention duration, content, and activities, designed to support families in meeting national recommendations were drawn from the intervention literature [30, 31] and our previous work [32–34]. Intervention “dose” (duration × time) was modeled after the successful adult-focused Diabetes Prevention Program [35] and the 2017 U.S. Preventive Services Task Force (USPSTF) evidence-based recommendations for weight loss, behavior change, and cardio-metabolic risk reduction in youth [36].

*EPIC El Rio Families* is intended for families served by El Rio Community Health Center (hereafter, El Rio), a Federally Qualified Health Center in the Southwestern United States serving more than 110,000 underinsured and uninsured patients, and a research partner in this study. El Rio patient demographics (85% Hispanic or Latina (84% White, 16% American Indian), 15% non-Hispanic (80% White, 11% Black, 6% Asian, 2% Pacific Islander, 1% American Indian); more than 90% will live at or below the federal poverty level) and our formative work [37] suggest that the study sample will be majority-Hispanic, of whom at least one-third will prefer to participate in Spanish-only groups. Prior to implementation, language and cultural adaptations of intervention content were guided by focus groups conducted with women patients of El Rio [37]. Findings from focus groups prompted translation of all materials into Spanish, delivery of the intervention by bicultural, bilingual coaches, and culturally-sensitive diet and physical activity recommendations that do not violate cultural beliefs and practices.

Intervention sessions will be group-based, attended by up to 15 mother-child dyads, and led by a minimum of two trained bilingual FQHC health and wellness staff. Each session is approximately 2 h in length and was designed for delivery over 16 consecutive weeks at one of two El Rio locations. Total duration was shortened to 13 weeks following formative research to accommodate school and holiday scheduling demands, with optional booster sessions following the core 13-week program.

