### Evaluation of the *EPIC El Rio Families* Study

This study uses a group randomized design to compare two groups of mothers who have had GDM or have been diagnosed with prediabetes, along with their children, who are between 8- and 12-years-old. The goal is to recruit 60 mother/child dyads to either the EPIC El Rio Families intervention or wait-listed control conditions. To identify potential participants with histories of GDM and/or prediabetes who are patients at El Rio, we will query the FQHC’s electronic health record (EHR). Women with a history of GDM during any of their pregnancies and/or a prior diagnosis of prediabetes and who have children 8- to 12-years-old at time of study will be contacted by phone and mail and invited to participate in *EPIC El Rio Families*. The participating child must be a biological child but does not have to be the direct product of a pregnancy with GDM. With attention to the composition of the FQHC patient population, the study sample will reflect majority Hispanic women from lower income groups.

Two El Rio clinics (A and B) have been selected to participate in this pilot study. Randomization to the intervention and wait-list control conditions will be performed *by site* using flip of a coin. Randomization by site has the least potential for contamination during the initial delivery period. Upon confirming respondent eligibility and obtaining written informed consent/assent, the research coordinator will match participants to the intervention site geographically nearest to their home, assign a study ID, and schedule baseline measurements. Following measurements, intervention participants will begin the 13-week face-to-face group program immediately, whereas the wait-listed controls will receive information about the offer to participate in the intervention after the first implementation and that they will continue to receive standard of care including access to nutritional counseling if desired. After 13 weeks, the intervention participants will transition to a follow-up phase while the wait-listed controls will begin the intervention (Fig. 1). Blinding is not possible with this design.

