Secondary behavioral outcomes associated with weight trajectory and T2DM risk in children and mothers will be assessed at 13 weeks (post-intervention) and 26 weeks (follow-up/weight maintenance). Child dietary intake will be assessed with *two, nonconsecutive*, interviewer-administered *24-h dietary recalls* conducted telephonically by trained nutritionists and entered into the Nutrient Data System for Research (Minneapolis, MN, v. 2012) [50]. Overall diet quality and its components (total vegetables, whole fruit, whole grains, plant, animal, and seafood proteins, fats, sodium, sugar, and refined grains) will be calculated using the Healthy Eating Index-2015, a valid and reliable measure of diet quality designed to assess the degree to which an individual’s intake conforms to dietary recommendations [51, 52]. Child moderate to vigorous physical activity and sedentary behavior will be assessed using the *Youth Activity Profile,* a self-administered 7-day (previous week) recall questionnaire validated for use in children ages 8- to 12-years-old [53] that includes 15 items divided into three sections: activity at school, activity out-of-school, and sedentary. Sleep behavior will be assessed using the *Children’s Sleep Habits Questionnaire, Abbreviated*, a 22-item survey designed for parent report of key child sleep domains that encompass major medical and behavioral sleep disorders in school-aged children [54]. Maturity will be assessed from a self-report of Tanner’s breast/genital and pubic hair descriptions. The validated questionnaire presents illustrations of developmental stages shown to agree with pubertal staging by a physician [55].

Parental dietary intake will be assessed using the validated *Arizona Food Frequency Questionnaire*, a self-administered semi-quantitative 159-item questionnaire in which respondents report how often they typically consume specific foods and food groups and associated portion sizes in the past 3 months [56, 57]. Parent physical activity will be assessed using the validated *Arizona Activity Frequency Questionnaire*, a self-administered 59-item questionnaire in which participants report whether they performed each activity during the past 28 days [58]. Primary outputs include daily energy expenditure (kilocalories), number of hours per day spent in each activity, and number of activities reported for each category.

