Given the feasibility focus of this study, we will also evaluate whether aspects of the intervention work as intended, including participant *acceptability* (participant satisfaction) and program *relevance* (rated using brief surveys of the relevance of the intervention to daily life, promoters and barriers to program attendance and engagement, the degree to which families report using the intervention to guide behavioral choices, and surveys of lifestyle coaches trained to deliver the intervention). We will assess *adoption* by El Rio and *integration with the existing clinical setting* using semi-structured interviews with El Rio wellness staff and administrators and *feasibility* (of delivery by providers and FQHC) by examining recruitment, enrollment, and retention rates, session attendance data, and observed participant engagement with intervention activities. *Fidelity* will be assessed through observation of research staff following an established rubric, and *program costs* will be evaluated using a bottom-up micro-costing approach (including direct medical and non-medical costs including personnel gross hourly salaries, intervention material costs, and overhead costs related to use of facilities for prevention services will be tracked and analyzed in partnership with El Rio’s data team members). We will also explore the *potential for replication and dissemination* using semi-structured interviews with El Rio wellness staff assigned to coordinate and deliver the program, and administrators and advisory board members who understand how to align the intervention with El Rio’s fiscal and strategic plans, and who have relationships with other FQHCs in Arizona and nationally. Our a priori focus on factors influencing *sustainability* (e.g., reach, integration with other health/wellness programs, institutionalization) beyond the research funding period will remain a major consideration throughout the proposed study.

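### The blinding sentence is too broad: families and coaches cannot be blinded, but the telephone interviewers for the children's diet recalls need not know clinic or arm

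*Protocol article*

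**What the plan says.** All references are to the protocol article. Under the heading Evaluation of the EPIC El Rio Families Study it sets out the allocation: "Randomization to the intervention and wait-list control conditions will be performed" by site, with two clinics and a coin flip. Participants are then placed by geography: "the research coordinator will match participants to the intervention site geographically nearest to their home, assign a study ID, and schedule baseline measurements". The paragraph closes on the sentence at issue: "Blinding is not possible with this design". It does not separate families, coaches, outcome assessors and analyst.

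The same section later describes the child diet outcome as two non-consecutive, interviewer-administered 24-hour recalls, "conducted telephonically by trained nutritionists and entered into the Nutrient Data System for Research". These recalls feed the Healthy Eating Index-2015 and its components. They are secondary: "Secondary behavioral outcomes associated with weight trajectory and T2DM risk in children and mothers will be assessed at 13 weeks", and again at 26 weeks.

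The curriculum section assigns delivery to others. Sessions are "led by a minimum of two trained bilingual FQHC health and wellness staff".

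**The concern.** A 24-hour recall depends on how the interviewer probes for portions and forgotten foods. An interviewer who knows that a child is in the programme may probe differently, without intending to. The curriculum promotes vegetables, whole grains and legumes and discourages added sugar. The diet index scores vegetables, whole grains and sugar among its components. Differential probing could therefore act on the very items that the programme targets.

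If the sentence is followed literally, the study gives up a safeguard that site randomisation does not preclude. The trial is a pilot meant to supply estimates for a larger one, so a distorted diet estimate could be carried forward.

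**Working it through.** The point rests on comparing statements. The only arithmetic is a count.

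**1. Whom does the design prevent from being masked?**
- Families: they either attend face-to-face sessions or wait. They cannot be masked.
- Coaches: they deliver the sessions. They cannot be masked.
- Research staff near the sessions: fidelity "will be assessed through observation of research staff following an established rubric", so some research staff may see sessions. Not all research staff can be masked.
- Telephone nutritionists: they work by phone, away from the clinics. The article gives them no part in delivery, and nothing in site randomisation or a wait-list requires them to know the clinic.

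**2. What would reveal the arm to an interviewer?** With one clinic per arm, the clinic's name is the arm. The research coordinator assigns the study ID when matching a family to a site, and the article does not say whether the ID encodes the site. Masking therefore needs a call list without the clinic and an ID that does not carry it. A family can still disclose during the call.

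**3. Which outcomes are concerned?**
- Weight and height are measured with calibrated instruments.
- The mother's diet and activity questionnaires and the child's activity questionnaire are self-administered.
- Child sleep and the home environment are parent-reported.
- Among the behavioural outcomes, only the child recall is described as interviewer-administered.

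**4. How many recalls?** Inputs are the target of 60 dyads and two recalls per child. I assume two recalls at each time point, with full recruitment and no dropout.
- At 13 weeks: 60 x 2 = 120.
- Over both follow-up times: 60 x 2 x 2 = 240.

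The larger figure overstates the exposure. The article says "After 13 weeks, the intervention participants will transition to a follow-up phase while the wait-listed controls will begin the intervention". By 26 weeks both arms are due to have had the programme and differ mainly in timing. The clear contrast between treated and untreated children covers the 120 recalls at 13 weeks.

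**5. Can the bias be sized?** No. The article gives no mean, standard deviation, target difference or between-interviewer variance for any diet outcome. An illustration shows only what an assumed shift would do to the planned unadjusted two-sample t-test, with 30 children per arm.
- The standard error of a standardised difference is sqrt(2/30) = 0.258.
- Column two uses the noncentral t distribution with 58 degrees of freedom.
- Column three is a simulation of three groups of 10 per arm at an intra-group correlation of 0.15, the upper value in the power calculation.

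| Assumed shift (SD) | Rejection rate, correlation 0 | Rejection rate, correlation 0.15 |
|---|---|---|
| 0 | 5.0% | about 21% |
| 0.1 | 6.7% | about 22% |
| 0.2 | 11.9% | about 26% |
| 0.3 | 20.8% | about 33% |

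The shifts are assumptions with no source in the article, and the result depends heavily on the correlation. The table also ignores the mixed model that follows the t-test. It is not an estimate of this trial's error rate.

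**The case against.** The strongest reply is that the sentence follows directly on the account of how families are allocated and start or wait. Its natural subject is then families and delivery. The article says nothing for or against masking assessors, and call lists and coded datasets are details that a condensed article leaves to the full protocol. Part of this stands: the absence of such details is not a fault. But the sentence is an affirmative, unqualified statement about the whole design, and a reader planning the diet calls would take it as settling the matter.

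Several further objections stand and limit the point:
- The nutritionists' independence is an inference. The article does not say who employs them, what other contact they have with the trial, or what they are told.
- Masking them does nothing about the children's own reporting, which comes from unblinded participants.
- Diet is one of several secondary behavioural outcomes, and the primary outcome is instrument-measured.
- Masking the analyst is a separate and weaker matter. It guards against choices made in analysis and has no effect on interviewing. The article describes no analyst, and with one site per arm coded labels may be easy to decode.

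A reader might infer that the child diet results are biased, or that the false-positive rate rises to some stated level. The article supports neither. It leaves a risk open, and gives nothing from which to derive the bias's size or direction.

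**Conclusion.** The point holds in a limited form. The blinding sentence is correct for families and coaches and too broad beyond them. It leaves the child diet outcomes open to an interviewer bias that could be reduced, mainly in the roughly 120 recalls at 13 weeks.

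This rests on three assumptions: the nutritionists take no part in delivery, two recalls are taken at each time point, and recruitment reaches 60 dyads without loss. If the nutritionists turn out to be delivery staff, they cannot be masked and the point falls away for them.

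Importance is low. One secondary outcome in a pilot is affected, and the weight and BMI results are untouched.

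**What to change.** Replace the sentence with: *Families and coaches cannot be blinded. Telephone dietary-recall interviewers take no part in delivery, are not told clinic or arm, and receive study IDs that do not encode site; they ask families not to disclose participation and record any unmasking.* First confirm that the nutritionists have no role in the sessions.

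Optionally, and as a separate statement, add that the analyst works with coded arm labels where feasible.

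The cost is the wording, a call list without the clinic field, site-neutral IDs, a short request at the start of each call and a field for recording unmasking. No measurement or visit changes. Reporting how often interviewers were unmasked would let readers judge how well the masking held.

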**Fig. 1 Fig1:**
[figure not shown]
EPIC El Rio Families Participant Anticipated Enrollment and Study Design

This design is responsive to standards of care for T2DM prevention [44] and will provide the opportunity to investigate pre−/post-intervention effects, intervention versus control effects, and maintenance effects. The number of participants and design also allow us to evaluate processes critical to successful implementation by El Rio, informing future replication and the potential scaling of the intervention to other sites in this and other FQHC networks. This clinical trial (ClinicalTrials.gov identifier NCT03781102) has been approved by the University of Arizona Institutional Review Board and all participants will provide informed consent or assent prior to participation.

Changes in percent weight for the mothers and changes in the BMI z-score for the children are used to confirm that there is adequate statistical power with the sample size of *n* = 60 dyads. For mothers, the calculation is based on the observed change in the DEPLOY study for both sexes [34]. The mean change in body weight after 6 months was − 6.0% (standard deviation = 4.0%). For children, the calculation is based on data from the EPIC Kids Study in which the mean change in BMI z-score was 0.054 (standard deviation = 0.02) [32]. The power calculation assumed that in each period (intervention versus wait-list control) there will be 3 groups with 10 dyads per group (*n* = 30 intervention versus *n* = 30 wait-list control). The statistical power is > 80% for the mothers and 95% for the children assuming an intra-group correlation or 0.15 or below (two-sided alpha level of 0.05). As this is a pilot study to provide estimates for a larger trial, there is no adjustment for multiple comparisons.

The primary outcome is percent change in body weight and BMI at 13 weeks (post-intervention) and 26 weeks (follow-up/weight maintenance). Body weight and height will be measured using a calibrated, digital scale with a mechanical height rod and a stadiometer. Adult BMI is categorized using international classifications of BMI (overweight, 25–29.9 kg/m^2^; obese, > 30 kg/m^2^) [45]. In children, BMI percentile is determined using age- and sex-specific growth charts developed by the CDC in 2000 [46]. Lacking a gold standard for measuring change in weight status in children, we will use the recommended BMI z-score change, which has been established as a good proxy for fat mass z-score change [47]. Child and adult waist circumference, linked to metabolic syndrome in both populations, will be measured at the umbilicus. All measures will be completed in duplicate, and the average of the two measures will be used. Secondary physiological outcomes in children and mother**s** include changes in blood pressure and hemoglobin A1c (HbA1c). These data will be collected using portable, CLIA approved technologies. The definition of hypertension will be adjusted for age per national guidelines [48, 49].

.

Secondary behavioral outcomes associated with weight trajectory and T2DM risk in children and mothers will be assessed at 13 weeks (post-intervention) and 26 weeks (follow-up/weight maintenance). Child dietary intake will be assessed with *two, nonconsecutive*, interviewer-administered *24-h dietary recalls* conducted telephonically by trained nutritionists and entered into the Nutrient Data System for Research (Minneapolis, MN, v. 2012) [50]. Overall diet quality and its components (total vegetables, whole fruit, whole grains, plant, animal, and seafood proteins, fats, sodium, sugar, and refined grains) will be calculated using the Healthy Eating Index-2015, a valid and reliable measure of diet quality designed to assess the degree to which an individual’s intake conforms to dietary recommendations [51, 52]. Child moderate to vigorous physical activity and sedentary behavior will be assessed using the *Youth Activity Profile,* a self-administered 7-day (previous week) recall questionnaire validated for use in children ages 8- to 12-years-old [53] that includes 15 items divided into three sections: activity at school, activity out-of-school, and sedentary. Sleep behavior will be assessed using the *Children’s Sleep Habits Questionnaire, Abbreviated*, a 22-item survey designed for parent report of key child sleep domains that encompass major medical and behavioral sleep disorders in school-aged children [54]. Maturity will be assessed from a self-report of Tanner’s breast/genital and pubic hair descriptions. The validated questionnaire presents illustrations of developmental stages shown to agree with pubertal staging by a physician [55].

Parental dietary intake will be assessed using the validated *Arizona Food Frequency Questionnaire*, a self-administered semi-quantitative 159-item questionnaire in which respondents report how often they typically consume specific foods and food groups and associated portion sizes in the past 3 months [56, 57]. Parent physical activity will be assessed using the validated *Arizona Activity Frequency Questionnaire*, a self-administered 59-item questionnaire in which participants report whether they performed each activity during the past 28 days [58]. Primary outputs include daily energy expenditure (kilocalories), number of hours per day spent in each activity, and number of activities reported for each category.

The home food and physical activity environment will be assessed using the *Family Nutrition and Physical Activity Tool,* a 21-item survey of the family home environment and practices associated with children’s risk of becoming overweight. Parents will use the tool to report the frequency of breakfast and family meals, modeling of nutrition, nutrient dense foods and high calorie beverages, restriction and reward, parent modeling physical activity, child’s physical activity, screen time, TV in bedroom, and sleep routines [59, 60].

Given the considerable impact of social and environmental factors on participants’ ability to follow through with health recommendations, we will collect demographic and socioenvironmental data associated with T2DM risk and health disparities (e.g., food insecurity, housing stability, culture and language, community support, socioeconomic status, financial barriers, literacy and numeracy) using the PRAPARE questionnaire developed for use in health care settings, and already routinely implemented by El Rio. All surveys will be made available in English and Spanish.

The intention-to-treat principle will be used for all the analyses. Differences in participants’ baseline characteristics between the two groups will be evaluated by a two-sample *t*-test for continuous outcomes and by Chi-square test or Fisher’s exact test for categorical outcomes. Initial analyses will compare the changes between baseline and follow-up between the intervention versus wait-list control groups using two-sample sample *t*-tests. Subsequently, a mixed-model analysis of covariance including treatment group, time, and baseline value of the outcome will be used to assess the effects of intervention at 13 and 26 weeks. Participants will be treated as a random effect nested within group. An interaction effect between time and treatment group will be assessed first. If there is no interaction effect, the overall treatment difference will be assessed. Otherwise, the treatment difference will be assessed at each time point. In order to measure the relative cost-effectiveness of these programs, we will also explore costs associated with implementation by El Rio staff.

Given the feasibility focus of this study, we will also evaluate whether aspects of the intervention work as intended, including participant *acceptability* (participant satisfaction) and program *relevance* (rated using brief surveys of the relevance of the intervention to daily life, promoters and barriers to program attendance and engagement, the degree to which families report using the intervention to guide behavioral choices, and surveys of lifestyle coaches trained to deliver the intervention). We will assess *adoption* by El Rio and *integration with the existing clinical setting* using semi-structured interviews with El Rio wellness staff and administrators and *feasibility* (of delivery by providers and FQHC) by examining recruitment, enrollment, and retention rates, session attendance data, and observed participant engagement with intervention activities. *Fidelity* will be assessed through observation of research staff following an established rubric, and *program costs* will be evaluated using a bottom-up micro-costing approach (including direct medical and non-medical costs including personnel gross hourly salaries, intervention material costs, and overhead costs related to use of facilities for prevention services will be tracked and analyzed in partnership with El Rio’s data team members). We will also explore the *potential for replication and dissemination* using semi-structured interviews with El Rio wellness staff assigned to coordinate and deliver the program, and administrators and advisory board members who understand how to align the intervention with El Rio’s fiscal and strategic plans, and who have relationships with other FQHCs in Arizona and nationally. Our a priori focus on factors influencing *sustainability* (e.g., reach, integration with other health/wellness programs, institutionalization) beyond the research funding period will remain a major consideration throughout the proposed study.

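### The children's 95% power does not follow from its printed inputs, which give about 99.8%, and it rests on an implausibly small SD of 0.02 that needs checking

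*Protocol article*

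**What the plan says.** The sample-size paragraph is in the protocol article under Methods/design, Evaluation of the EPIC El Rio Families Study, after Fig. 1. It uses two source studies to support 60 dyads as adequate.

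- **Mothers:** "The mean change in body weight after 6 months was − 6.0% (standard deviation = 4.0"%).
- **Children:** "the mean change in BMI z-score was 0.054 (standard deviation = 0.02"). No sign or direction is printed.
- **Clustering:** in each condition "there will be 3 groups with 10 dyads per group", so 30 against 30.
- **Correlation and alpha:** "assuming an intra-group correlation or 0.15 or below (two-sided alpha level of 0.05").
- **Result:** "The statistical power is > 80% for the mothers and 95% for the children".

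The article labels 0.02 a standard deviation. It gives no sample size for the children's source study and does not say what change is assumed in the control arm for either mothers or children.

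**The concern.** There are two separate problems.

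1. **The output does not match the inputs.** The mothers' standardised effect is 1.5 SD with power just over 80%. The children's is 2.7 SD in the same design, and that should give power very close to 100%, not 95%.

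2. **The SD itself looks wrong.** If individual changes were roughly normal with mean 0.054 and SD 0.02, about 99.7% of children would move in the same direction. That is not credible for individual change in BMI z-score under a behavioural programme. A ratio of 2.7 is the size one expects of an estimate divided by its standard error, so 0.02 could be a standard error that was carried over as an SD.

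The missing sign adds to the doubt about how the figures were transcribed. Read literally, 0.054 is an increase, although the abstract names reduction in excess body weight as the primary outcome.

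BMI z-score change is the children's measure of the primary weight outcome and one of the two supports for the sample size. If the SD is too small, a null result in children could be read as evidence of no benefit from a well-powered comparison. The same SD could also be carried into planning the larger trial that this pilot is meant to inform.

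**Working it through.** **Inputs (all from the sample-size paragraph).** Mothers: change 6.0, SD 4.0. Children: change 0.054, SD 0.02. Three groups of 10 per arm (30 against 30), ICC 0.15 (the upper limit stated), two-sided alpha 0.05.

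**Formulas.**
- Design effect: DE = 1 + (10 − 1) × 0.15 = 2.35.
- Standard error of the difference: SE = SD × √(2 × 2.35/30) = 0.396 × SD.
- Non-centrality: ncp = change/SE. Power comes from the non-central t distribution.
- Degrees of freedom: 2 × (3 − 1) = 4 for a cluster-level test, or 60 − 2 = 58 if participants supply the degrees of freedom.

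**Step 1: mothers.** SE = 4.0 × 0.396 = 1.583 and ncp = 6.0/1.583 = 3.79. Power is 80.6% on 4 df and 96.1% on 58 df. Both satisfy the stated lower bound of 80%, and the 4-df result sits right at it.

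**Step 2: children, inputs as printed.** SE = 0.02 × 0.396 = 0.00792 and ncp = 0.054/0.00792 = 6.82. Power is 99.8% on 4 df and above 99.99% on 58 df. A smaller ICC only raises it. The stated 95% is not reproduced.

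**Step 3: what would give 95%.** On 4 df at ICC 0.15, 95% needs one of: an SD of about 0.028, a change of about 0.039, or an ICC of about 0.39. Multiplying the SD by √2 gives 94.2% for the children, but the same step puts the mothers at 53%, so it cannot be the common method.

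**Step 4: plausibility of the SD.** 0.054/0.02 = 2.7, and Φ(2.7) = 0.9965. The central 95% of changes would be 0.054 ± 1.96 × 0.02, or 0.015 to 0.093.

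**Step 5: sensitivity to the SD (change 0.054, ICC 0.15).**

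| SD | Power, 4 df | Power, 58 df |
|---|---|---|
| 0.02 | 99.8% | about 100% |
| 0.03 | 92% | 99% |
| 0.04 | 72% | 92% |
| 0.05 | 54% | 77% |
| 0.10 | 19% | 27% |

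Power drops below 80% once the SD exceeds about 0.036 (4 df) or 0.048 (58 df).

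**Step 6: conditional scenario.** Suppose 0.02 is a standard error from n children. Then SD = 0.02 × √n. The article does not give n, so 10 to 100 is an assumption.

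| Assumed n | SD | ICC 0.15: 4 df / 58 df | ICC 0: 4 df / 58 df |
|---|---|---|---|
| 10 | 0.063 | 38% / 56% | 70% / 90% |
| 20 | 0.089 | 22% / 32% | 43% / 63% |
| 50 | 0.141 | 12% / 16% | 21% / 31% |
| 100 | 0.200 | 8% / 10% | 13% / 18% |

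**The case against.** **The "The statistical power is > 80% for the mothers and 95% for the children" sentence may carry one inequality for both figures.** If the sign before 80% also governs 95%, then 99.8% is compatible and the mismatch disappears. This stands as a possibility. It leaves the SD untouched.

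**The demonstrable gap runs upward.** On the printed inputs, 95% understates the power. This stands: the mismatch is not evidence of low power.

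**The 4-df method is not documented.** The mothers' figure is an open lower bound that a 58-df test also meets. This stands too, which is why both are shown. Neither gives 95% for the children.

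**Rounding.** An SD just under 0.025 would print as 0.02 and gives about 97.7% on 4 df. That narrows the gap without closing it.

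**Direction and control arm.** The sign has no effect on two-sided power, and the use of a change instead of a between-arm difference applies equally to the mothers. Both are points of clarity, not arithmetic faults in the children's figure.

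**It is a pilot with a feasibility focus.** That lowers the stakes, and no analysis depends on the 95%. But the paragraph offers the calculation as confirmation of adequate power, so the figure should be sound.

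A reader might infer that the children's power is probably far below 95%. The article does not support that: it calls 0.02 a standard deviation, gives no source sample size, and leaves the standard-error reading as an inference that only the source study can settle.

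**Conclusion.** The children's 95% does not follow from the printed inputs. They give about 99.8% on 4 df and about 100% on 58 df at ICC 0.15, unless 95% was meant as a lower bound. Either way the SD of 0.02 is implausibly small for individual change, and the power claim holds only if the SD is nearly that small.

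Low power is a conditional conclusion. If 0.02 is a standard error from an assumed 10 to 100 children, power at ICC 0.15 is about 38% down to 8% (4 df) or 56% down to 10% (58 df). It is higher at smaller ICC, reaching about 70% or 90% at ICC 0 with 10 children. It would therefore be too strong to say that the trial cannot detect the planned effect. What is established is that a figure used to support the sample size is unsound as written and should be rechecked.

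**What to change.** 1. Check 0.054 and 0.02 against the source study, and establish whether 0.02 is an SD or a standard error.
2. Use the between-child SD of BMI z-score change.
3. Print the direction of the change and the change assumed in the control arm.
4. Recompute with the cluster-level method used for the mothers, name that method and its degrees of freedom, and say whether the result is a lower bound.
5. Restate the children's power. Alternatively, replace it with the expected 95% confidence-interval half-width, which at ICC 0.15 on 4 df is 2.776 × 0.396 × SD = 1.10 × SD.

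The cost is consulting one source and rewriting a few sentences. Enrolment does not change. The stated power may become less favourable.
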